**Fig. 1 Fig1:**
[figure not shown]
SPIRIT diagram for BARGASTRO. Legend: AE: Adverse Event,: BAROS: Bariatric Analysis and Reporting Outcome System, QoL: Quality of Life, VAS: Visual Analogue Scale, SAE: Serious Adverse Event, Handling assessment of the suture material by the surgeon regarding the different dimensions using a Likert Scale (1 excellent, 2 very good, 3 good, 4 satisfied, 5 poor). In the case of conventional suture the following dimensions will be assessed: pliability, tissue drag, knot security, knot run down, knot pull tensile strength, anastomosis approximation, overall impression. In case of the barbed suture material the dimensions: pliability, pass through the tissue, traumaticity of the barbs, anchoring capacity of the barbs, perception of the locking system, anastomosis approximation, overall impression will be judged. EQ5D5L questionnaire consists of 2 parts - a descriptive system including the following 5 dimensions: mobility, self-care, usual activities, pain or discomfort, anxiety or depression, which are rated on a 5 point level scale (1=no problem, 2=slight problems, 3=moderate problems, 4=severe problems and 5= extreme problems), - and the EQ-VAS containing a scale from 0 to 100, on which the patient records his/her actual health status (0 (the worst you can imagine) and 100 (best health you can imagine). BAROS questionnaire includes three main categories: percentage of excess weight loss, changes in medical conditions, and quality of life. The quality of life questionnaire comprises the following dimensions (self-esteem, physical activity, social contacts, work conditions, sexual activity and eating behaviour) scored by the patient on a 10 point Likert scale

## Methods: participants, interventions, and outcomes

### Study setting {9}

Patients will be recruited in a consecutive manner in one German Academic University Hospital (UKSH, Department of General, Visceral, Thoracic, Transplant and Paediatric Surgery, Kiel, Germany), which is familiar and well trained in the application of barbed and conventional threads as well as in robotic-assisted Roux-en-Y gastric bypass surgery. Approximately, 40,000 patients are treated in this hospital and 2300 within the Department of General, Visceral, Thoracic, Transplantation and Paediatric Surgery, and 80–100 robotic Roux-en-Y gastric bypasses are performed annually, revisional bariatric bypass procedures excluded (10–15 per year). The clinic has been selected to exclude a learning curve.

### Eligibility criteria {10}

#### Inclusion criteria

Patients being at least 18 years of age with a BMI ≥ 40 kg/m^2^ or with a BMI ≥ 35 kg/m^2^ combined with one or more of the following comorbidities: refractory arterial hypertension, type 2 diabetes mellitus, and/or proven sleep apneoa scheduled for an elective, primary robotic-assisted gastric bypass surgery with the need to approximate the gastro-jejunal anastomosis (GJA) and the jejuno-jejunal anastomosis (JJA) were eligible for participation.

#### Exclusion criteria

Emergency surgeryPrevious gastric surgeryHistory of chronic steroid usePregnancy or breastfeeding.Patients with hypersensitivity or allergy to the suture materialNoncomplianceParticipation in another RCT study

### Who will take informed consent? {26a}

Experienced and trained physicians of the Department of General, Visceral, Thoracic, Transplant and Paediatric Surgery, UKSH, Kiel, Germany, will screen the patients for eligibility. Patients who meet the inclusion criteria will be asked for their willingness to participate in the BARGASTRO study and will be informed by the physicians with verbal and written information about the purpose of the study, the operation modalities, and their benefits and risks. The written informed consent has to be obtained from each agreed participant in accordance with the origins of the Declaration of Helsinki and before any study procedure occurs. The participants are recruited several weeks before RYBG surgery.

### Additional consent provisions for collection and use of participant data and biological specimens {26b}

Due to the Data Protection Law (GDPR), which has been effective in Europe since 25 May 2018, a written informed consent has to be provided by each patient for the collection and usage of individual patient data.

## Interventions

### Explanation for the choice of comparators {6b}

An effective construction of the intestinal anastomoses is of major importance. The intestinal anastomosis can be performed using interrupted or continuous sutures or staples to prevent complications. Using suture materials for the loss of tension due to suture loosening is an important issue. To maintain the tension, a constant traction by the assistance and repeated tightening of the suture is necessary. The anchoring properties of a barbed suture material obviate the need for a conventional surgical knot and provide tissue approximation and traction without requiring an assistant, thus improving surgical efficiency. In addition, barbed sutures prevent suture slipping, enable tieless and speedy, and secure anastomosis approximation. This is especially beneficial in minimally invasive procedures, where constraints of space and manoeuvrability may present special technical challenges, especially in robotic surgical interventions, where no assistance controls and pulls the suture material regularly. Therefore, in the present study, the performance of a new unidirectional barbed thread is compared to a conventional one in robotic-assisted RYGB. Both selected suture materials are approved and carry the CE-mark. In addition, both devices are applied in their intended use.

#### Unidirectional barbed suture (UBS) description

The barbed suture material investigated in the current study is named Symmcora^®^ mid-term and is manufactured by B. Braun Surgical SA, 08191 Rubi, Barcelona, Spain. It is a sterile synthetic, mid-term absorbable monofilament symmetric anchoring device made from a copolymer of 72% glycolide, 14% *ε*-caprolactone, and 14% trimethylene carbonate, comprising an elongate main body (core) with anchoring elements that provide a knotless wound closure capacity to the device, intended for secure fixation in tissue without using knots. In the current study, the barbed suture material is used in its unidirectional configuration. Here, a single group of anchors is placed along the elongated body, being the wound closure device provided with a locking system at the distal end, opposite to the longitudinal direction the anchors point out (Fig. 2). The diameter refers to the unbarbed section length near the needle attachment area. The diameter in the needle-attachment zone of Size_n_ is equivalent to the diameter of Size_n+2_ having the same USP designation.

**Fig. 2 Fig2:**
[figure not shown]
Schematic drawing of the unidirectional configuration of the barbed thread

Biocompatibility tests have shown that the unidirectional barbed suture is non-cytotoxic, non-mutagenic, non-genotoxic, non-toxic, non-pyrogenic, non-irritating, non-sensitizing, and biocompatible. The suture tensile strength is 87% after 7 days and 51–57% after 14 days. Mass absorption of the device is essentially complete after approximately 90–120 days post-implantation.

#### Conventional suture (CS) description

As a comparative suture material, Novosyn^®^ manufactured by B. Braun Surgical SA, 08191 Rubi, Barcelona, Spain, was chosen. It is a sterile synthetic absorbable braided surgical suture composed of a copolymer made from 90% glycolate and 10% L-lactate. The suture material is metabolized to glycolic and lactic acid by hydrolysis. About 75% of the original tensile strength remains after 14 days of implantation, about 40–50% after 21 days, and about 25% after 28 days. The suture is completely absorbed by hydrolysis within 56–70 days.

### Intervention description {11a}

All RYBG surgeries will be carried out as usual and according to the local standard using the da Vinci Xi Surgical System (Intuitive, Sunnyvale, CA, USA). Gastrojejunostomy (GJ) and jejuno-jejunostomy (JJ) in the Novosyn^®^ Group are performed in the same way as the GJ and JJ of the Symmcora^®^ Group. Randomization occurs after the creation of the side-to-side linear stapler anastomosis. Then, the enterotomy is closed by a continuous, running seromuscular suture. GJ is usually created with two threads starting from the corners. The JJ is usually with one thread. There is no difference regarding the procedure if Novosyn^®^ or Symmcora^®^ is used.

#### Experimental group = unidirectional barbed suture group (UBS)

In the unidirectional barbed suture group (UBS group), two barbed threads of USP 2/0, 15 cm, and violet with a HR 26-mm needle will be applied. The first stitch of the first thread is performed in the left lateral corner of the enterotomy, with the inclusion of the staple line. After completion of one-half of the anastomosis, a second thread is started from the right corner. The last 2–3 stitches with each thread are guided in the opposite direction to anchor the suture in the tissue and to dispense with the need for a knot. The threads are cut at an appropriate length to avoid local adhesions.

Proximal to the anastomosis, the small intestine is separated with a linear stapler. A Roux limb of 150 cm is measured, and a side-to-side linear stapled jejuno-jejunostomy is created again using a linear stapler. The enterotomy is closed by a single running suture using the unidirectional barbed thread of USP 3/0, 15 cm, and violet with a HR 26-mm needle. After completion of the anastomosis, a methylene blue test of the gastrojejunostomy, the check for blood dryness, the repositioning of the omentum majus, and the installation of a drainage are regularly carried out.

#### Control group = conventional suture group (CS group)

To complete the gastrojejunostomy, conventional threads of USP 2/0, 45 cm, violet, and with a HR 26-mm needle are used (two threads), and to complete the jejuno-jejunostomy, one conventional thread of USP 3/0, 45 cm, violet, and with a HR 26-mm needle will be applied. For the gastrojejunostomy and jejuno-jejunostomy, the suture starts and ends with a knot in comparison to the UBS group. Two threads are applied and knotted at the corner of the gastrojejunostomy. Two threads are sutured in the opposite direction and will be knotted together at the middle of the complete suture. The jejuno-jejunostomy is closed with a single running suture.

### Criteria for discontinuing or modifying allocated interventions {11b}

Exit criteria will be as follows: (1) RYGB is not possible to be performed due to severe adhesions, (2) intraoperative decision to perform a gastric sleeve instead of a RYGB, and (3) intraoperative decision to modify the procedure due to visceral obesity, hepatomegaly, or adhesions.

### Strategies to improve adherence to interventions {11c}

Before the start of the trial, an initiation visit was performed in the clinic by the study management to inform and instruct the involved personnel on the study-specific documents and procedures. The surgeons and nurses will document the collected data directly in a paper-based case report form. The documentation is checked on a regular basis by a research monitor to verify adherence to the study protocol and to perform source data verification. Already during the inpatient clinic stay, each patient receives the appointment for the follow-up examination in writing by the study personnel. To standardize both suture groups, suture material from the same batch is packed in the opaque randomization envelopes. After surgery, a randomization fax is sent by the clinic to the sponsor to report the successful inclusion of a patient in combination with the randomization result.

### Relevant concomitant care permitted or prohibited during the trial {11d}

No suture material or suture technique other than described in the protocol can be used for GJA and JJA construction. Any protocol violation has to be clearly described and reported. Postoperative care is performed in accordance with the clinical standard, which includes the following parameters, but these will not be reported and collected in the CRF: same-day surgery, single-shot antibiotic prophylaxis, perioperative pneumatic compression, early mobilization, ulcus prophylaxis (Pantozol 40 mg), thrombosis prophylaxis (Innohep 50 IE/kg), early oral food intake, nutritional advice, intramuscular vitamin B12 substitution, and length of hospital stay ranging from 1 to 4 days.

### Provisions for posttrial care {30}

N/a. Reason: patients are treated in accordance with the clinical routine; all complications occurring during the study will be treated in accordance with the hospital’s treatment protocol.

### Outcomes {12}

Collection of the study outcomes will be performed preoperatively (baseline clinical data, demographics, eligibility), intraoperatively (randomization, closure time, suture handling, surgical details), at day of discharge, 30 days, and 12 months postoperatively. Figure 1 lists the primary and secondary outcomes including the measurement time.

#### Primary outcome

Time (in minutes) to perform the gastro-jejunal and jejuno-jejunal anastomosis using a stopwatch is the primary endpoint. Time starts when the needle passes the tissue the first time and ends when the needle is cut from the thread. The time to perform both the GJA and the JJA (rounded to the nearest full minute) will be the total anastomosis time.

#### Secondary outcomes

The rate of anastomosis leaks, anastomosis stenosis, gastric fistula, obstruction, anastomosis bleeding and re-anastomosis, and the frequency of other complications according to Clavien–Dindo will be collected as safety variables until discharge, 30 days, and 12 months postoperatively [38].

In addition, the operation duration, costs, length of hospital stay, patient satisfaction, pain, and quality of life will be compared in both suture groups and over time.

Length of hospital stay is defined as the period from day of surgery until day of discharge. Cost assessment includes the costs of suture material, costs per operation minute, number of used threads, and costs per hospital day. Pain evaluation will be performed by the patient using the visual analogue scale (VAS), which is a numeric scale ranging from 0 (no pain) to 100 (maximal pain). In addition, patients will be asked by the surgeon for their postoperative satisfaction using a numeric scale from 0 (not satisfied) to 100 (maximal satisfaction). Quality of life will be analysed using the EQ-5D-5L questionnaire, which is a standardized measure of health status developed by the EuroQol Group to provide a simple, generic measure of health for clinical and economic appraisal [39]. The questionnaire consists of a descriptive system comprising five dimensions (mobility, self-care, usual activities, pain or discomfort, anxiety, or depression) and the EQ visual analogue scale (EQ-VAS). Each dimension has five levels: 1 = no problem, 2 = slight problems, 3 = moderate problems, 4 = severe problems, and 5 = extreme problems. The result of the assessment of all five dimensions leads to the so-called EQ index, which ranges from 1 minimum to 5 maximum. Using the EQ-VAS, each patient records his/her healthy status ranging from 0 (the worst health you can imagine) to 100 (best health you can imagine). The EQ5D5L is used in the German language, and a licence has been obtained by the sponsor from EuroQol–Group. 


Handling of the suture material will be judged by the participating surgeons after each surgery using a questionnaire including different categories with five evaluation levels (excellent, very good, good, satisfied, poor), and the outcome for both suture types (barbed vs. conventional) will be compared. The following categories will be assessed in the case of the conventional suture material (pliability, tissue drag, knot security, knot run down, knot pull tensile strength, anastomosis approximation, overall impression). The assessment of the barbed suture includes the following dimensions: pliability, pass through the tissue, traumaticity of the barbs, anchoring capacity of the barbs, perception of the locking system, anastomosis approximation, and overall impression.

### Participant timeline {13}

An overview of the time schedule and study measurements per visit is shown in Fig. 1.

### Sample size {14}

The sample size calculation is based on the primary endpoint “time to perform the GJA and JJA” to show superiority of a unidirectional barbed suture compared to a conventional suture material. Several studies have been published analysing both types of suture materials regarding this outcome parameter [6, 7]. The weighted group means and the weighted pooled standard deviations were calculated based on the results of the subset of four studies [24–27] providing suturing times to create the GJA. Considering 14.20 min to approximate the GJA in the barbed suture group compared to 16.10 min in the conventional group, a sample size of 71 patients in each suture group will have 80% power to detect a mean difference of −1.90 min assuming that the common standard deviation is 4.00 using a two-sample *t*-test with a 0.05 two-sided significance level. Including a drop-out rate of 5%, the sample size becomes up to 75 patients in each suture group, a total of 150 patients. The times to create the JJA are only reported in two studies [25, 27] with great differences. Therefore, to calculate the sample size for the current study, the time for the construction of the JJA was not taken into account. In addition, it was previously mentioned that the times for JJA formation did not differ between traditional and barbed sutures [6]. For sample size calculation, nQuery Advisor^®^7.0 was used.

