## Statistical methods

### Statistical methods for primary and secondary outcomes {20a}

The intention-to-treat principle will be applied for data analysis. A CONSORT diagram will be utilized to graphically display the eligibility, allocation, and follow-up course of the participants (**41**). Demographics, anamnesis, and baseline characteristics will be presented in a tabular form by treatment group. Continuous measures will be summarized by the number of non-missing observations, minimum, maximum, median, and mean with standard deviation, and categorical measures by absolute and relative frequencies.

The primary outcome measure is the suturing time to perform the GJA and JJA. The independent samples *t*-test with a two-sided significance level of 0.05 will be used for the comparison of treatment groups (UBS vs. CS). 95% CI will be provided to allow a quantitative evaluation of the treatment effect with respect to the minimum clinically relevant difference of 1.9 min. The secondary variables will be analysed descriptively.

The test regarding the primary variable is considered confirmatory; all other tests are explanatory. For the analysis of binary data, a chi-square test will be used; for nonparametric data, a *U*-test according to Wilcoxon–Mann–Whitney or to Kruskal–Wallis will be used; and a *t*-test or one-way ANOVA will be used for metric data, if a normal distribution is assumed. All statistical tests will be performed two-tailed with a pre-specified significance level of *α* = 5%. Two-sided 95% confidence intervals will be given, where appropriate.

The secondary outcomes include the following:
Pain (visual analogue scale, values from 0 to 100, 100—max. pain)Satisfaction (numeric scale values from 0 to 100, 100—best)EQ-5D-5L questionnaire: EQ index range from 1 best to 5 worse and EQ-VAS scale value (0–100—best).BAROS questionnaire, three sub-scores with a maximum of 3 points each (weight loss (% of excess), improvement of medical conditions and Quality of Life), and the total score with a maximum of 9 points (best).Length of hospital stay in daysHandling assessment of the suture material (different dimensions using a Likert scale with levels from 1 excellent to 5 worse).

The outcomes will be analysed descriptively and compared between suture groups and between visits, where appropriate.

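### The 80% power is worked out for gastro-jejunal time alone and is unsupported, and probably optimistic, for the total anastomosis time that carries the only confirmatory test

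*Protocol article*

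**What the plan says.** Under Primary outcome, the endpoint covers both joins: "The time to perform both the GJA and the JJA (rounded to the nearest full minute) will be the total anastomosis time". Statistical methods {20a} compares this time between arms with one independent-samples t-test, which is the only confirmatory test.

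Sample size {14} opens by tying the calculation to that combined endpoint. Its inputs are narrower: "Considering 14.20 min to approximate the GJA in the barbed suture group compared to 16.10 min in the conventional group", pooled from four studies that report GJA suturing times. The calculation proceeds "assuming that the common standard deviation is 4.00"; at a two-sided alpha of 0.05, 71 patients per arm are said to give 80% power for a difference of 1.90 min. A 5% drop-out allowance brings 71 to 75 per arm, 150 in total.

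The section then says of the JJA: "Therefore, to calculate the sample size for the current study, the time for the construction of the JJA was not taken into account". Two reasons are given. Only two studies report JJA times, and they differ greatly. Also, "it was previously mentioned that the times for JJA formation did not differ between traditional and barbed sutures".

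Finally, Statistical methods {20a} says the confidence interval for the primary endpoint will be read "with respect to the minimum clinically relevant difference of 1.9 min".

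**The concern.** The variable that was powered is not the variable that will be tested. The reason given for leaving out the JJA does not repair this. If JJA time is the same with either suture, adding it to GJA time leaves the expected difference at 1.90 min but brings in the JJA's own spread. A t-test on the total then has a smaller standardised effect than the one planned for, unless the two times offset each other within patients.

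Two things are at stake. A non-significant result on total time could be read as coming from a trial with 80% power when that was never shown for total time. And the confidence interval for total time would be judged against 1.9 min, a figure that appears in the protocol only as a planning difference for the GJA.

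**Working it through.** **Inputs from Sample size {14}.** GJA means 14.20 and 16.10 min, difference 16.10 − 14.20 = 1.90; SD 4.00; two-sided alpha 0.05; 71 per arm; 5% drop-out. The reported JJA effect is taken as 0 min. The SD of JJA time (s) and its within-patient correlation with GJA time (r) are not in the document and are assumptions below.

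**Step 1: reproduce the stated figure.** Noncentrality = 1.90 / (4.00 × √(2/71)) = 2.83 on 140 degrees of freedom. The exact two-sample t-test gives 80.3% power at 71 per arm and 79.7% at 70, so 71 is the smallest size that reaches 80%. Drop-out: 71 / 0.95 = 74.7, so 75. The arithmetic is correct for GJA time.

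**Step 2: SD of the total.** SD_total = √(4.00² + s² + 2·r·4.00·s). This exceeds 4.00 whenever s² + 8·r·s > 0, that is, unless r is below −s/8. At s = 2 the correlation would have to be below −0.25.

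**Step 3: power for total time.** Difference held at 1.90 min, exact t-test:

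| Assumed s (min) | Assumed r | SD_total (min) | Power, 71 per arm | Power, 75 per arm |
|---|---|---|---|---|
| 1 | 0 | √17 = 4.12 | 77.8% | 80.1% |
| 2 | 0 | √20 = 4.47 | 71.0% | 73.4% |
| 2 | 0.3 | √24.8 = 4.98 | 61.7% | 64.1% |
| 3 | 0 | √25 = 5.00 | 61.4% | 63.8% |
| 3 | 0.5 | √37 = 6.08 | 45.6% | 47.6% |

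**Step 4: detectable difference.** Power depends on the ratio of difference to SD, so the difference that keeps about 80% at 71 per arm is 1.90 × SD_total / 4.00. This is 1.90 × 4.12 / 4.00 = 1.96 min in the first row and 1.90 × 6.08 / 4.00 = 2.89 min in the last: about 2.0 to 2.9 min.

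**Step 5: what would restore 80%.**
- *A negative correlation.* At r = −0.3, power at 71 per arm is 83.7% for s = 1 and 82.2% for s = 2.
- *A true JJA saving.* The amount needed is 1.90 × SD_total / 4.00 − 1.90. That is 2.12 − 1.90 = 0.22 min at s = 2, r = 0, and 2.375 − 1.90 = 0.475, about 0.5 min, at s = 3, r = 0.

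**Step 6: the 1.9 min threshold.** It equals the pooled literature difference for the GJA. The document shows no separate derivation for total time and no clinical rationale.

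**The case against.** The strongest reply is that nothing is hidden. Sample size {14} labels the means as GJA times, says the JJA was left out and gives reasons. That stands as far as it goes. What remains wrong is the opening claim that the calculation is based on the combined endpoint, and disclosing the omission does not carry the 80% over to total time.

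Several further replies also have weight:

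- **The loss may be small.** The JJA is usually closed with one thread against two for the GJA, so a small JJA SD is credible. The endpoint is measured during surgery, so later drop-out should cost it little and a size near 75 is realistic. At s = 1, r = 0 that gives 80.1%.
- **The JJA effect may not be zero.** The Discussion reports no significant difference, which is weaker than none, and in this trial only the control JJA is knotted. A saving of 0.2 to 0.5 min could be enough (Step 5). It would restore power for a total effect larger than 1.9 min, not for the 1.9 min the protocol names.
- **The SD of 4.00 is itself borrowed.** The Background describes the comparative literature as laparoscopic. The trial is robotic, at one experienced centre, so its GJA spread could be lower or higher.

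The type I error of the test and the effect estimate are unaffected, and the planned 95% CI limits over-reading of a null result.

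A reader might also infer that 1.9 min was never a clinical judgement. The matching numbers suggest it, but the full protocol is not shown and may justify the value. If the JJA effect is truly zero, a minute saved on the GJA is also a minute saved in total. What can be said is that no rationale for total time appears here.

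**Conclusion.** The point holds as a mismatch between the powered and the tested variable. The stated 80% is correct for GJA time and is not shown for total GJA + JJA time, where it is probably optimistic. With no JJA suture effect and the assumed SDs and correlations of Step 3, power at 71 per arm lies between 78% and 46%. The size of the loss cannot be fixed from the document, because neither the JJA SD nor the correlation is given.

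A reader might go further and conclude that the trial is definitely underpowered for its primary endpoint. The document does not support that: a small JJA SD with 75 evaluable per arm, a clearly negative correlation or a modest true JJA saving would each leave power at or near 80%. It would also be too much to say that a GJA test is already planned. The Discussion promises only that GJA and JJA times will be reported separately.

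The use of 1.9 min as a relevance threshold for total time needs a justification or a new label, whatever the JJA SD proves to be.

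**What to change.** 1. Reword the opening of Sample size {14} so that the 80% power is stated for GJA time only.
2. Restate the power, or the difference detectable with 80% power, for total time. Use the blinded pooled SD of the total times already collected, supplied by data management without allocation so that the statistician stays blinded. Two-thirds of patients had been randomised when the article was prepared, and the endpoint is recorded in theatre, so the data exist. An SD taken across both arms together slightly overstates the within-arm SD: a true difference of 1.90 min adds (1.90/2)² = 0.90 to the variance. Say so next to the figure.
3. In Statistical methods {20a}, describe 1.9 min as the GJA planning difference, unless a clinical justification for total time is given.
4. Report the between-group GJA difference with a 95% CI as a supportive, non-confirmatory analysis. This extends the separate reporting already promised in the Discussion and matches the sample-size assumption.

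The cost is wording in two sections, one SD calculation and one supportive analysis on data already recorded. No extra patients and no change of primary endpoint are needed. The downside is that the stated power will probably look less favourable.
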